# Abstract

**Background** Worldwide, lesbian, gay, bisexual, transgender and intersex (LGBTI) people contend with high risks for HIV infection, stigma and discrimination, and for exclusion from HIV and other health services. In many low- and middle-income countries, LGBTI people are often hidden, marginalised and difficult to assess as part of general population-based surveys. Thus, assessing their exposures and outcomes and burden of HIV disease is extremely challenging. This presents a dilemma for HIV surveillance as their omission from surveillance systems leaves significant gaps in our understanding of HIV epidemics.

**Objective** This research project is aimed at conducting an observational, non-interventional, global cross-sectional internet survey in LGBTI participants to examine how various demographic, economic, socioecological, homophobic, psychosocial, attitudinal and behavioural variables potentiate HIV risk behaviour. We likewise aim to examine self-reported HIV prevalence, exposure to HIV related stigma and discrimination, and to study the association between these socioecological parameters and HIV care and treatment coverage in the survey participants.

**Methods** We imply internet sampling method to conduct the cross-sectional survey recruiting consenting adult LGBTI participants. We select internet sampling for it demonstrated to be particularly useful for hard-to-sample populations, higher number of respondents among hard-to-reach populations, faster recruitment, lower operational cost, greater level of anonymity and security provided to participants. Acknowledging selection bias, we may apply techniques, e.g. prediction modelling, to correct for the bias that results from differential access to, and use of, the internet. To safeguard the data privacy, rights and welfare of the research participants, the access to the online survey will be provided via anonymous weblink. The survey will be opened for three (3) months. Our cross-sectional study is observational by nature and it does not alter the exposure status of the consenting respondents and thus warrants minimal to no risk for the participants. We will examine the outcome and the exposures in the target population and will study their association. Our survey questionnaire provides essential components to fulfil the above objective and was developed using selected standard protocols.

**Key words** LGBTI, stigma, discrimination, HIV, health, socioecological, cross-sectional, behavioural, Internet, survey

# Research Protocol

## Introduction

### Background

An understanding of HIV burden, risk factors, and coverage of prevention and treatment services is critical for combatting the HIV epidemic. Behavioural surveys assessing these parameters are integral components of a national HIV strategy and surveillance system. Countries that implement repeated behavioural surveys can monitor changes in their populations' risks for HIV, determinants of those risks, and access to prevention and treatment over time.

Many individuals at high risk for HIV are socially marginalized, experience stigma and discrimination, and may not identify themselves as such when accessing services. This makes it difficult to track them in HIV programme registers and hinders efforts to assess the effectiveness of services, their exposures and outcomes. Such populations include LGBTI people, who are at increased risk for HIV infection compared with the general population at large. The underlying reason is that HIV prevalence among their sexual or needle-sharing network is already high. Although members of the general population also engage in frequent vaginal and anal sex without condoms, their chance of having an HIV-infected partner is much lower. Additionally, global prevalence of HIV among MSM is 19 times higher than in the general population, and prevalence among transgenders is 48 times higher.

### Rationale for the research

Behavioural surveillance among LGBTI populations is a priority in all epidemic settings. HIV control efforts directed at high-risk populations can have a substantial impact on the epidemic. HIV policies and programmes will be more effective if they are informed by measures of HIV prevalence among those populations, trends in their HIV-related risk behaviours, and the extent to which they access HIV and other health related services. This makes this survey a critical undertaking for monitoring the HIV epidemic and evaluating HIV control efforts.

Policies that criminalize behaviours of high-risk populations or limit their access to HIV and other health related services may further elevate their risk of acquiring and transmitting HIV. The infringement of human rights, verbal and physical violence and denial of health services associated with stigma and discrimination based on sexual orientation and gender identity is a demonstrated public health issue. Stigma is a central driver of morbidity and mortality at a population level[1]. Communities facing enacted sexual stigma are more likely to engage in sexual risk behaviours[2, 3]. They are less likely to adhere to their antiretroviral treatment[4] and have lower HIV testing rates[4-10]. Internalized homonegativity is associated with lower levels of HIV testing and lower levels of condom use[11]. A socio-ecological approach to health-related behaviour[12] allows for studies of the role of stigma related to sexual orientation and gender identity in their broader structural and social dimensions[1, 13, 14]. Most studies of homophobia have focused on the individual level. Being able to identify the level of homophobia at country level is important to guide public health policies as recent evidence shows that reductions in the homophobic climate are associated with improved health outcomes[15]. Data related to structural factors, such as the existence of legislation against LGBTI human rights, are generally available, although unevenly among low- and middle-income countries. But there is a lack of individual and interpersonal data on members of the LGBTI community in low- and middle-income countries.

The ultimate purpose of this research is to facilitate the collection and the analysis of socioecological data in consenting 18+ year-old LGBTI participants that could inform public health action in favour of these communities. This research proposal describes design and methods for conducting this cross-sectional web-based behavioural survey. The project is using a socioecological approach to data analysis, where the behaviour is viewed as being determined by individual, interpersonal and structural factors[12, 16-19].

## Methods and Design

### a) The scientific design of the study

#### *The survey objectives*

This research project is aimed to:

- conduct a cross-sectional observational, non-interventional, internet survey in consenting 18+ year-old LGBTI participants using an anonymous web-based self-administered questionnaire without any geographical restrictions;
- examine correlates of HIV infection to understand how survey variables, such as demographic, economic, socioecological, homophobic, psychosocial, attitudinal and behavioural, potentiate HIV risk behaviour and access to and uptake of HIV care and treatment services;
- provide evidence in favour of more LGBTI-inclusive health and HIV service delivery, advocacy, and policymaking.

### *Target population support for the survey*

We engaged with the LGBT Foundation and the members of the target population to seek their input on survey content to ensure that the survey design is consistent with on-the-ground realities, and to further encourage target population participation.

### *Ethical consideration*

The study protocol was assessed and approved by the Research Board of Ethics of the University of Aix-Marseille, and by the WHO Research Ethics Review Committee (ERC). See [appendix 2](#).

### *Funding*

The LGBT Foundation is supporting the research with in-kind contribution of USD 565.000. UNAIDS is providing an additional USD 45,240 from its core budget.

### *Timing and intervals between the survey rounds*

This is the first edition of the global LGBTI survey. Future annual edition of the survey will be determined after the evaluation of the 2019 edition. A tentative timeline for this survey can be found in appendix 3.

One interest of eventual annual editions of the survey is to study the changes and the evolution of key variables over time per country. The study does not track respondents year after year. It will analyse how indicators such as well-being, mental health, HIV self-prevention, homophobia for example are evolving following changes in LGBTI legislation, in government, or in the economy at country level.

This is similar as other surveillance. It typically does not include the same participants in repeat surveys. Ideally, behavioural surveys should be conducted at intervals in order to capture changes in risk behaviours and the HIV epidemic over time. This survey can therefore serve as a baseline for any future undertakings.

### *Questionnaire development*

The questionnaire of the survey contains established instruments for collecting survey data among key populations, such as LGBTI people, using validated questions and scores. These instruments include questions that have been used throughout the world; thus, their continued use will enable researchers to compare survey results across countries. The standardized instruments provided with these guidelines were designed to be self-administered using electronic or web-based data collection methods.

The questionnaire was built on the following four principles:

1. The process must preserve the complete anonymity of respondents. The privacy and security of respondents must be ensured at every step of the survey;
2. Questionnaire should be as short as possible. Only questions that are necessary should be included;
3. Filling out the online questionnaire should expose participants to no more than minimal risk, such as minimal discomfort, minimal anxiety;
4. Questions selected should have their reliability and validity already demonstrated and their collection should enable triangulation with other surveys.

We followed the following **key steps in questionnaire development**:

- decided on methods for questionnaire administration;
- determined investigation topics (questionnaire domains);
- developed and adapted the questionnaire;
- conducted cognitive testing;
- pre-tested the questionnaire;
- pilot tested the survey tool.

The content of the questionnaire is harmonized with standard indicators and protocol checklists used in behavioural surveillance. The questionnaire is organised as modules focused on topics, such as:

- demographics
- time preference, risk aversion
- socioeconomic status, including a question on financing hormones for transgender people
- behaviours increasing vulnerability to HIV infection (e.g. unprotected receptive anal intercourse, buying sex, selling sex, sharing nonsterile injecting equipment, alcohol and drug use)
- stigma and discrimination in the community, at workplace and health facility (sexual orientation, gender identity, HIV)
- internalized homophobia
- violence
- general health status
- mental health, including depression
- social support network, including family
- HIV prevalence, access to HIV and other health services, HIV services uptake:
  - knowledge of serostatus
  - eligible but not on HIV treatment
  - viral load suppression
  - unsuppressed viral load
  - currently in care
  - currently on antiretroviral therapy

- discussed pre-exposure prophylaxis
- use of pre-exposure prophylaxis
- health-care stigma

The consensus questionnaire (see [appendix 1](#)) consists of three modules:

- 1st module for LGBTI people, comprising 45 questions;
- 2nd module for MSM and transgender people, comprising 15 questions;
- 3rd module on HIV stigma, comprising 22 questions.

It was our preference to start and finish the survey with relatively comforting questions and statements to reduce any unforeseen discomfort in the participants.

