- ☐ 1 lowest social standing in my community

44. You would say you live in:

- ☐ a major city
- ☐ a medium- or small-size city
- ☐ a village
- ☐ a farm or an isolated house

45. People are different in their sexual attraction to other people. Which best describes your feelings? are you...

- ☐ attracted to other men or gay
- ☐ attracted to other women or lesbian
- ☐ attracted to both men and women or bisexual
- ☐ Straight or heterosexual
- ☐ I don't know

*Note: respondents answering 1 (gay), 3 (bisexual) or 5 (I don't know) will be offered to complete module 2*

*Respondents answering 2 (lesbian) or 4 (straight) will be redirected to question 61 (do you know your HIV status?)*

[ module 2 for gays, bisexuals, transgenders or men attracted to other men ]

exit

The following few questions are more specific for gay, bi, transgender and men attracted to other men

☐ OK *(click is required)*

An exit button is always available at the beginning of each module. Respondent can always scroll back to it

[Section on HIV prevention and exposure to HIV infection]

46. In the past 3 months, with how many **different** sexual partners did you have **anal sex without any kind of HIV prevention method**? That is without condoms, PrEP or an undetectable HIV viral load?
- ☐ 0
  - ☐ 1, steady
  - ☐ 1, casual
  - ☐ 2
  - ☐ 3 to 10
  - ☐ more than 10
  - ☐ Does not apply to me
47. Thinking about your last **anal sex partner without any kind of HIV prevention method** (that is without condom, PrEP or an undetectable viral load), how did it go?
- ☐ my partner fucked me (I was receptive)
  - ☐ I fucked him/her (I was insertive)
  - ☐ I both fucked and got fucked (I was both receptive and insertive)
  - ☐ does not apply to me
48. Thinking about your last **anal sex partner without any kind of HIV prevention method** (that is without condom, PrEP or an undetectable viral load), did you know his HIV status? tick as many as apply
- ☐ I didn't ask
  - ☐ s/he's HIV negative
  - ☐ s/he's HIV positive and I don't know his/her viral load
  - ☐ s/he's HIV positive AND undetectable
  - ☐ I was on PreP
  - ☐ s/he was on PreP
  - ☐ I don't remember
  - ☐ I had more than one partner and I do not know everyone's HIV status
  - ☐ does not apply to me

49. In the last 3 months, how much of the sex you've had with men has been under the influence of alcohol or any other drug?

- ☐ none of it
- ☐ almost none of it
- ☐ less than half
- ☐ about half
- ☐ more than half
- ☐ almost all of it

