- ☐ all of it
- ☐ does not apply to me

50. In the past 3 months, did you share drug injecting equipment (needles, syringes) with someone else?

- ☐ yes, once
- ☐ yes, several times
- ☐ no, I don't share my equipment
- ☐ no, I don't inject drugs

51. What do you do if your potential date/sexual partner tells you they are is HIV positive? (tick as many as you like)

- ☐ I do not see them again
- ☐ I am not comfortable having sex with them
- ☐ I am comfortable having sex with them because we use a condom, I am on PrEP and/or he is undetectable
- ☐ I'm HIV positive too

52. In the last 12 months, how often have **you paid someone** to have sex with you?

- ☐ never
- ☐ 1-2
- ☐ 3-10
- ☐ 11-50
- ☐ more than 50 times

53. In the last 12 months, how often have **you been paid** to have sex

- ☐ never
- ☐ 1-2
- ☐ 3-10
- ☐ 11-50
- ☐ more than 50 times

54. I feel comfortable in gay bars

- ☐ 7 strongly agree
- ☐ 6
- ☐ 5
- ☐ 4 undecided
- ☐ 3
- ☐ 2
- ☐ 1 strongly disagree
- ☐ does not apply

55. Social situations with gay men make me feel uncomfortable

- ☐ 7 strongly agree

- ☐ 6
- ☐ 5
- ☐ 4 undecided
- ☐ 3
- ☐ 2
- ☐ 1 strongly disagree
- ☐ does not apply

56. I feel comfortable being seen in public with an obviously gay person

- ☐ 7 strongly agree
- ☐ 6
- ☐ 5
- ☐ 4 undecided
- ☐ 3
- ☐ 2
- ☐ 1 strongly disagree
- ☐ does not apply

57. I feel comfortable discussing homosexuality in a public situation

- ☐ 7 strongly agree
- ☐ 6
- ☐ 5
- ☐ 4 undecided
- ☐ 3
- ☐ 2
- ☐ 1 strongly disagree
- ☐ does not apply

58. I feel comfortable being sexually attracted to other men

- ☐ 7 strongly agree
- ☐ 6
- ☐ 5
- ☐ 4 undecided
- ☐ 3
- ☐ 2
- ☐ 1 strongly disagree
- ☐ does not apply

59. Homosexuality is morally acceptable to me

- ☐ 7 strongly agree
- ☐ 6
- ☐ 5
- ☐ 4 undecided
- ☐ 3
- ☐ 2
- ☐ 1 strongly disagree
- ☐ does not apply

60. Even if I could change my sexual orientation, I wouldn't

- ☐ 7 strongly agree

- ☐ 6
- ☐ 5
- ☐ 4 undecided
- ☐ 3
- ☐ 2
- ☐ 1 strongly disagree
- ☐ does not apply

61. Do you know your HIV status?

- ☐ I'm HIV-negative
- ☐ I'm HIV-positive
- ☐ I don't know
- ☐ I don't want to answer

- ☐ PREV (*clicking here brings the respondent to earlier module in case she/he would like to change*)
- ☐ DONE (*brings the respondent to a thank you message*)

*Note: participants that have answered "I'm HIV-positive" at question will be offered to participate to module 3 (see next page)*

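### PrEP discussion and PrEP use are listed as questionnaire topics, but no question measures either, and Q48 offers PrEP and undetectable answers that its own stem rules out

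*Protocol*

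**What the plan says.** Protocol, Methods and Design, section a), Questionnaire development, states: "The content of the questionnaire is harmonized with standard indicators and protocol checklists used in behavioural surveillance". It then introduces a list with "The questionnaire is organised as modules focused on topics, such as". Two of the closing entries are "discussed pre-exposure prophylaxis" and "use of pre-exposure prophylaxis". The same section gives the size of the instrument: a first "module for LGBTI people, comprising 45 questions", a second "module for MSM and transgender people, comprising 15 questions", and a third module on HIV stigma with 22 questions. It refers to Appendix 1 for the questionnaire itself.

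In Appendix 1, Q46 to Q48 concern anal sex with no HIV prevention method, defined as no condom, no PrEP and no undetectable viral load. The Q48 stem asks about the last such partner: "that is without condom, PrEP or an undetectable viral load), did you know his HIV status". Its tick-all answers include the respondent having been on PrEP, the partner having been on PrEP, and the partner being HIV-positive with an undetectable load. Q51, on reactions to a potential partner who discloses HIV, has one option reading "I am comfortable having sex with them because we use a condom, I am on PrEP and/or he is undetectable". The note after Q45 sends respondents who answer lesbian or straight past module 2 to Q61, which is the first question on the respondent's own HIV status.

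**The concern.** A topic list that refers the reader to the questionnaire should be matched by questions. If two listed topics have none, the survey cannot deliver them. The loss would be permanent for this round: section o) says there is no possibility of giving participants further direct information once they have completed the questionnaire, and section a) presents this round as a possible baseline for later ones.

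The Q48 conflict is a separate matter of data quality. The objectives include understanding HIV risk behaviour, and the topic list names unprotected receptive anal intercourse as one such behaviour. Q47 is the item that records receptive role. A respondent who answers Q47 and then ticks PrEP or an undetectable partner at Q48 has described an event that neither stem was meant to capture.

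**Working it through.** No sample-size or power figure bears on this point. The check is an item-by-item reading of Appendix 1 against the topic list.

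1. **Is the questionnaire complete as shown?** The stated module sizes sum to 45 + 15 + 22 = 82. The numbering agrees: Q1–Q45 is 45 questions, Q46–Q60 is 60 − 46 + 1 = 15, and Q61–Q82 is 82 − 61 + 1 = 22. Q1 is the mandatory consent click described in section c), and Q2 to Q82 are printed. No substantive question is missing from the text.

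2. **Where does PrEP occur in Appendix 1?**
   - Stems of Q46, Q47 and Q48 (3 items): each time as part of the definition of sex without prevention, so as an exclusion.
   - Answer options of Q48: own PrEP and partner's PrEP, both ruled out by the stem.
   - One answer option of Q51: own PrEP joined by and/or to condom use and a partner's undetectable status.
   - Health-service items Q29–Q31 and module 3 (Q61–Q82): no mention.

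3. **Can either topic be derived?**
   - PrEP discussion: 0 of 82 questions.
   - PrEP use: 0 of 82 dedicated questions. Q48 cannot supply a numerator, because its event excludes PrEP. Q51 cannot, because its option does not separate the three methods. A zero at Q46 cannot serve as a proxy either, because it mixes condoms, PrEP, undetectable status and no anal sex. Respondents who skip module 2 see no item that mentions PrEP at all.

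4. **What does a conflicting tick at Q48 show?** Q47 and Q48 name the same event, the last partner without prevention, so a PrEP or undetectable tick at Q48 contradicts the event recorded at Q47. The link to Q46 is looser. Q46 counts partners over three months, whereas Q47 and Q48 have no time window. A PrEP user may answer zero or not applicable at Q46 and still tick own PrEP at Q48, and is then not misclassified at Q46. If Q46 shows exactly one partner, the last such partner must be that one, and the answers can be compared. If Q46 shows two or more, one last-partner answer says nothing about the others.

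5. **Can the error be sized?** The falsely unprotected share at Q46 would be roughly p × m, where p is the share using PrEP and m is the share of those who report covered sex there. The document gives neither. Purely as assumptions, 2% × 10% gives 0.2 percentage points and 20% × 50% gives 10, a 50-fold range. Even that presumes that none of these respondents had another, truly unprotected partner.

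**The case against.** The list is introduced as examples of topics, not as a ranked set of indicators. As printed, the two PrEP lines stand outside the sub-list on HIV services uptake, though that may be a layout effect. No objective and neither of the two research questions names PrEP, so no stated analysis fails outright. This limits the weight of the point, but an illustrative list still should not name two topics that are absent.

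On Q48, the protocol promises discrepancy flags for inconsistent answers (Exclusion and Non-qualifiers) and case-by-case treatment of multiple-choice questions (Sample size). Recoding detail may properly sit in an analysis plan that is not shown. That stands for handling the conflicting ticks. It does nothing for PrEP discussion and use, where there is nothing to recode.

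A reader might infer that everyone ticking those Q48 options is wrongly counted as unprotected at Q46 and Q47, and that this biases the main risk outcome in line with access to services. The document does not support that. A tick shows an inconsistency without showing which answer is wrong, no scoring rule is given, the protocol does not single out Q46 or Q47 as its main outcome, and nothing in it shows that PrEP users misread the stem more than others.

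**Conclusion.** The point holds as a mismatch between the topic list and the instrument, together with an internal contradiction in Q48. The first part is certain and needs no assumption: neither PrEP topic can be reported from the questionnaire as printed. The second part is certain as a wording conflict. Its consequence, protected sex recorded as unprotected at Q47 and possibly at Q46, is a possibility whose size the document does not allow one to estimate. The sample-size figures are unaffected. This should be corrected before the survey opens.

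**What to change.** - **Add one PrEP item directly after Q61**, shown to respondents who do not answer that they are HIV-positive, with the answers: never discussed; discussed, not using; using now; used in the past. HIV status is first asked at Q61, so this routing cannot be applied earlier, and the position also reaches those sent past module 2. The protocol asks for questions of demonstrated validity, so an established wording should be used if one is available.
- **Make the Q48 stem and options agree**, for example by asking about the last anal sex partner without a condom, so that PrEP and undetectable become valid answers. Q47 names the same event, so its stem should change in step if the two answers are to stay linked.
- **If Q48 stays as it is**, flag these ticks as discrepant and run the Q47 analysis with and without them. Do the same for Q46 only where a single partner is reported. Do not use a last-partner answer to overwrite a count of several partners.
- **If no item is added**, delete the two PrEP topics from the list.

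The cost is one short item on a survey averaging 11 minutes, a reworded stem (two if Q47 follows), and translation with back-translation. The protocol names 17 languages including English, so 17 − 1 = 16 translations. Deleting the two topics instead costs two lines, but leaves the Q48 conflict to be settled.
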